• Patients will be recruited consecutively from the participating CR centres. • When the patient first visits the CR centre, one of the members of staff will screen the patient for symptoms of depression and anxiety. • If the patient has a positive score on depression and/or anxiety and complies with the additional inclusion criteria and none of the exclusion criteria, CR staff will inform the patient orally and in writing about the study. • Two scenarios are then possible: 1. If the patient is interested in participating in the study and does not wish additional time to contemplate the decision or to have a significant other present, informed consent will be signed by both parties. 2. If the patient is interested in participating in the trial and wishes either 24 h to contemplate the decision and/or to have a significant other present, they receive a link to a declaration of consent via e-boks. • After having signed the informed consent (the patient will receive a copy) the patient will be included into the study. • A note will be added to the patient’s electronic health records, if the patient is included into the study. • A link to the questionnaire to complete at baseline will be sent to the patient via e-boks. • When the therapist has received a confirmation that the questionnaire has been completed, and if the HADS score is still positive, the patient will be contacted by telephone by the therapist and take part in a short purpose-designed diagnostic interview. • Within 2 days, eligible patients are randomised to either TAU *or* TAU + the *eMindYourHeart* intervention by administrative staff from SDU and informed of the result by the therapist. • Patients allocated to TAU + the *eMindYourHeart* intervention will receive instructions on how to use/access the platform by the therapist. • Patients who do not wish to participate in the study are asked about *(i)* the reason and *(ii)* whether we may use the patient’s data from the rehabilitation settings and DHDR.	

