## Ethics and safety considerations

Ethical approval for the trial is obtained from the Regional Committees on Health Research Ethics for Southern Denmark [S-20180024] (version 5 approved 10 September 2019). The required permissions are obtained from the Danish Data Protection Agency via Odense University Hospital (17/41433 on November 24, 2017). The trial will be conducted according to the Helsinki Declaration and was prospectively registered on http://www.clinicaltrials.gov [NCT04172974]. All patients will receive oral and written information about the trial and sign an informed consent form. Patients who do not wish to participate in the trial are asked about *(i)* the reason and *(ii)* whether we may use the patient’s data from the rehabilitation setting and the Danish Cardiac Rehabilitation Database (DHRD). DHRD is a Danish quality database that collates health data on CR from all hospitals in Denmark to ensure cohesiveness and quality in CR in Denmark [36]. It is compulsory for all hospitals offering CR to report into the database.

Subjects can leave the trial at any time for any reason if they wish without any consequences. The investigator can decide to withdraw a subject from the trial due to urgent medical reasons. Subjects withdrawn from the trial will not be replaced and will not be followed-up. Subjects who drop out of the trial will be followed up according to the intention-to-treat principle [37].

There are no expected medical risks associated with trial participation, as medical treatment is provided according to national clinical guidelines [14] and the trial compares two types of care (i.e., *(i)* TAU + eHealth intervention versus *(ii)* TAU. However, we cannot rule out that the eHealth intervention may induce additional depression and anxiety in some patients [38]. The Ethics Committee does not require us to have a Data Safety Monitoring Board (DSMB), but annually we are required to report serious side effects and incidents to the Committee.

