**Table 2 Tab2:**
[figure not shown]
Overview of the modules of the *eMindYourHeart* intervention

Psychologists will interview patients randomised to the intervention arm over the phone, using motivational interviewing and a brief purpose-designed interview protocol that includes elements from the Schedules for Clinical Assessment in Neuropsychiatry (SCAN) interview. The purpose of the interview is to gain information about the patient and the patient’s situation, equivalent to a standard anamnestic assessment.

Patients are expected to complete the intervention within a 12-week period. All patients will have access to the intervention up to 6 months post intervention, enabling patients to revisit the material and reuse it ad libitum. The intervention is protocolised by means of a treatment manual to ensure fidelity and is somewhat flexibly targetable to the individual patient’s needs and preferences. These include adding additional time to the treatment from the standard 9 weeks all the way to 12 weeks, helping patients with sleep and lifestyle changes through the extra (optional) modules, giving specific psychological tools based on CBT to patients with needs not addressed in the standard treatment [e.g. stress management tools], and the possibility of extra phone calls.

Patients will gradually work through the modules and communicate with the psychologists via a secure online platform through asynchronous text messages. The therapist receives messages from the patient and notifications about the patient’s treatment course. Psychologists and master’s students in psychology from the University of Southern Denmark will provide the intervention. They are supervised by licensed psychologists, who are part of the project team. Internet-delivered treatment targets the same core treatment processes as in face-to-face treatment – only the mode of delivery is different [23].

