## Statistical methods

Data will be analysed according to the modified intention-to-treat principle (i.e., all patients with a 3-month evaluation will be analysed as randomised). The intention-to-treat principle will be applied from the time that patients have initiated treatment (i.e., after the brief interview protocol that includes elements from the SCAN interview and motivational interviewing). Categorical variables will be summarised as n (%), continuous variables as min-max, mean (SD), and median. All summaries will be by randomisation group. The primary analysis will be a linear regression of depression scores at 3 months including randomisation group and strata as factors and baseline depression scores as covariate. Potential confounders, apart from baseline and stratification variables, identified by clinical consensus, will be included in multivariable analyses when appropriate (e.g. when performing sub-group analyses). A mixed effects model will be used to analyse the longitudinal change in HADS scores and HeartQoL scores, adjusting for strata, incorporating random effects to model the homogeneity within cluster and the correlation within patient across time. Pre-planned subgroup analyses will be conducted for the primary outcome with respect to: *(i)* type of IHD (stable versus unstable); *(ii)* sex (female versus male); *(iii)* age (median split); *(iv)* depression status at baseline (< 10 versus ≥11; *≥11 is considered a moderate score*). A sensitivity analysis will be conducted. The statistical analysis will be transparent, subject to review and approval by the project team.

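### Intention-to-treat is said to start after an interview that appears to be held in the intervention arm only, which conflicts with analysing all patients with a 3-month evaluation as randomised

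*Protocol article*

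**What the plan says.** Five places in the protocol article bear on this point.

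- **Statistical methods, analysis set.** The analysis is called modified intention-to-treat, explained as "all patients with a 3-month evaluation will be analysed as randomised". This rule is the same in both arms and does not depend on starting treatment.
- **Statistical methods, next sentence.** "The intention-to-treat principle will be applied from the time that patients have initiated treatment (i.e., after the brief interview protocol". The interview is characterised there by its use of SCAN elements and of motivational interviewing. This moves the start of intention-to-treat to a later event.
- **Intervention, Contents (text after Table 2).** "Psychologists will interview patients randomised to the intervention arm over the phone, using motivational interviewing and a brief purpose-designed interview protocol", again with SCAN elements. This interview follows randomisation and is described for one arm.
- **Eligibility and recruitment, Table 1.** Once the baseline questionnaire is in and HADS is still positive, "the patient will be contacted by telephone by the therapist and take part in a short purpose-designed diagnostic interview". The next step listed is that "eligible patients are randomised to either TAU" or TAU plus the intervention. This interview precedes randomisation and applies to all. Neither SCAN nor motivational interviewing is mentioned.
- **Ethics and safety considerations.** "Subjects who drop out of the trial will be followed up according to the intention-to-treat principle". For patients whom the investigator withdraws, by contrast, "Subjects withdrawn from the trial will not be replaced and will not be followed-up".

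**The concern.** Intention-to-treat protects the comparison because membership of the analysis set is fixed at randomisation, before allocation can influence it. A start date that depends on a later event is harmless only if the event occurs, and is counted, in the same way in both arms. Here the event seems to exist in one arm only.

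Allocation is open to patients and therapists, so whether an intervention patient goes on to the interview can depend on knowing the allocation. The Limitations section itself says that some patients, for example depressed ones, may lack the motivation and energy to take part. If such patients leave the intervention arm before the interview and are not counted, while similar patients in the TAU arm are, the 3-month HADS depression means no longer compare like with like. The primary outcome is affected directly.

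**Working it through.** **Step 1: which interview marks the start?**

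| Feature | Statistical methods | Contents | Table 1 |
|---|---|---|---|
| SCAN elements | yes | yes | not mentioned |
| Motivational interviewing | yes | yes | not mentioned |
| Who | not stated | intervention arm | all still HADS-positive |
| Timing | at treatment initiation | after randomisation | before randomisation |

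The description in Statistical methods matches the Contents interview on both named elements. An interview held before allocation also fits poorly as the moment at which treatment starts. The match is strong, but it is an inference.

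**Step 2: consequence under each reading.**
- *Contents interview:* an intervention patient who leaves between allocation and interview falls outside the second rule. If that patient has a 3-month HADS score, the first rule includes the patient, so the two rules conflict. No equivalent event is defined for TAU-alone patients.
- *Table 1 interview:* everyone randomised has already passed it. There is no differential filter, but the sentence then adds nothing, and Contents contradicts Table 1 on who is interviewed and when.

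**Step 3: the plan's own sample size.** Inputs from Sample size calculation: SD 3.5, difference 2 points, power 90%, alpha 5% (taken as two-sided), dropout 30%.
- Normal approximation: 2 × (3.5 × (1.960 + 1.282) / 2)² = 64.4, so 65 per arm. The t test needs 66 (power 0.903).
- Dropout: 66 / 0.7 = 94.3, stated as 94 per arm; 2 × 94 = 188.

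The stated figures reproduce. They do not depend on this point and do not change with it.

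**Step 4: illustrative size.** Two inputs are assumptions, because the documents give neither:
- f, the share of the evaluable intervention arm (patients who have a 3-month HADS score) that the rule would exclude;
- D, how many points worse these patients would score at 3 months than those retained in that arm.

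The retained mean lies f × D below the full-arm mean, so bias = f × D. With 66 controls and 66 × (1 − f) intervention patients, SE = 3.5 × √(1/66 + 1/(66(1 − f))). The two-sided rejection rate under a true null is 1 − Φ(1.96 − bias/SE) + Φ(−1.96 − bias/SE).

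| f | D | Bias (points) | Share of 2-point difference | Type I error |
|---|---|---|---|---|
| 10% | 2 | 0.2 | 10% | 6.2% |
| 10% | 3 | 0.3 | 15% | 7.7% |
| 20% | 2 | 0.4 | 20% | 9.5% |
| 20% | 3 | 0.6 | 30% | 15.3% |

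For the last row, SE = 3.5 × √(1/66 + 1/52.8) = 0.646 and 0.6 / 0.646 = 0.93. At the mild end, f = 5% and D = 1 give a bias of 0.05 points and a type I error of 5.1%.

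**The case against.** The strongest defence is that the sentence just before the disputed one already defines the analysis set, equally for both arms and without reference to starting treatment. Nowhere does the article say outright that intervention patients who miss the interview are removed. A reader might infer that one-arm exclusion is the settled rule. The text does not support that; it supports a conflict between two adjacent sentences, one of which permits such exclusion.

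Second, the Contents and Table 1 interviews are both purpose-designed and held by telephone, and could be one event loosely described. If so, no filter arises. This cannot be ruled out, although the wording favours the other reading.

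Third, a reader might infer that TAU patients have no treatment to initiate. That is wrong: under Treatment as usual, all patients receive the rehabilitation programme. What is missing is a defined initiation event for TAU-alone patients.

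Fourth, dropouts are to be followed up under intention-to-treat, and non-responders stay enrolled. Both weigh against exclusion but do not settle it. Follow-up under the principle does not help if the principle starts only after the interview. The non-responder rule, in Definition of treatment adherence and dropout, covers patients who stop during treatment, not those who never start.

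Finally, the figures are illustrative, and 20% of the evaluable arm is a strong assumption. Non-starters without a 3-month score are lost under either rule, so only those with a score count towards f. Adjustment for baseline depression would remove part of the gap and change the SE; it would not remove selection on motivation. Keeping 66 in both arms would put the top figure near 17%, but the exclusion also shrinks the intervention arm, which gives 15.3%. These limits all stand.

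**Conclusion.** The point holds as a contradiction with a possible bias attached. Within Statistical methods, the second rule conflicts with the first. Across sections, the article is inconsistent about who is interviewed and when.

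The risk to the primary comparison is conditional: it arises if the start of treatment means the intervention-arm interview, which is the closer reading. The direction is plausibly in favour of the intervention, but the documents do not establish it. Nor do they give its size. The illustrative range of 0.2 to 0.6 HADS points, with type I error of about 6% to 15%, rests on the assumed shares and score gaps and is before baseline adjustment. An actual bias of that size should not be read into the plan.

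On either reading the sentence should go: on one it can filter a single arm after open allocation, on the other it is redundant. How patients without a 3-month evaluation are handled is a separate issue that affects both arms and is not settled here.

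**What to change.** 1. In Statistical methods, delete the sentence that starts intention-to-treat at treatment initiation.
2. State that intention-to-treat starts at randomisation in both arms, so that no patient with a 3-month evaluation is excluded for not starting treatment or for missing an interview.
3. Use any set restricted to patients who started treatment for supplementary analysis only.
4. Reconcile Table 1, Contents and Statistical methods: say whether there are one or two interviews, who receives each, and whether each comes before or after randomisation.

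**Cost.** Wording only; the target of 188 is unchanged. The estimated effect may become slightly smaller. The article does not say explicitly that intervention patients who never start are sent the 3-month questionnaire, so this should be confirmed. At the status date in the article, 31 of 188 patients had been included, so most of the data were still to come.

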**Methods:**

*eMindYourHeart* is a multi-center, two-armed, unblinded randomised controlled trial that will compare a therapist-assisted eHealth intervention to treatment as usual in 188 CR patients with IHD and comorbid depression or anxiety. The primary outcome of the trial is symptoms of depression, measured with the Hospital Anxiety and Depression Scale (HADS) at 3 months. Secondary outcomes evaluated at 3, 6, and 12 months include symptoms of depression and anxiety (HADS), perceived stress, health complaints, QoL (HeartQoL), trial dropout (number of patients dropped out in either arm at 3 months) and cost-effectiveness.

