#### Secondary objectives

The secondary objectives are to evaluate the efficacy of the eHealth intervention targeting depression and anxiety + TAU as compared to TAU alone on symptoms of anxiety, perceived stress, health complaints, QoL, and dropout (number of patients dropped out in either arms at 3 months) at 3 months, and symptoms of depression, anxiety, perceived stress, health complaints, and QoL at 6 and 12 months’ follow-up and cost-effectiveness/cost-utility.

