## Trial outcomes

Primary: Symptoms of depression, measured with HADS at the end of the intervention (i.e., 3 months).

Secondary: Symptoms of anxiety measured with HADS at 3 months; symptoms of depression and anxiety at 6- and 12 months’ follow-up; QoL (HeartQoL) at 3, 6, and 12 months follow-up; trial dropout (number of patients dropped out in either arms at 3 months) and cost-effectiveness/cost-utility.

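### The mixed model for HADS and HeartQoL names strata but not baseline as adjustment, which may cost secondary precision; separately, the sections disagree on whether perceived stress and health complaints are secondary outcomes

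*Protocol article*

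**What the plan says.** Statistical methods describes two efficacy models. The primary one is a linear regression of HADS depression at 3 months, "including randomisation group and strata as factors and baseline depression scores as covariate". The other covers the repeated measurements: "A mixed effects model will be used to analyse the longitudinal change in HADS scores and HeartQoL scores, adjusting for strata". Beyond that, it has random terms for clustering and for repeated measurements on the same person. Baseline is not mentioned for this second model. A later sentence on potential confounders names baseline and the stratification variables as two separate things, so the word strata cannot be read as including baseline.

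The secondary outcomes appear in three places:

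- **Secondary objectives**, at 3 months: "symptoms of anxiety, perceived stress, health complaints, QoL, and dropout". For later visits: "symptoms of depression, anxiety, perceived stress, health complaints, and QoL at 6 and 12 months’ follow-up and cost-effectiveness/cost-utility".
- **Abstract (Methods)**: perceived stress and health complaints are again among the secondary outcomes at 3, 6 and 12 months.
- **Trial outcomes**: besides anxiety at 3 months, dropout and the economic outcome, the list has "symptoms of depression and anxiety at 6- and 12 months’ follow-up; QoL (HeartQoL) at 3, 6, and 12 months follow-up". Neither perceived stress nor health complaints is there.

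Table 3 schedules HADS, HeartQoL, the Perceived Stress Scale and the Health Complaints Scale at baseline, end of treatment, 6 months and 12 months.

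**The concern.** The mixed model carries the HADS and HeartQoL comparisons beyond the primary one. The adjustment set stated for it lacks the covariate that usually explains most of the outcome variance and that the primary model uses. There are three ways to build such a model:

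1. Leave baseline out and compare follow-up scores.
2. Treat baseline as a first visit with its own mean in each arm, so that the effect is a difference in change.
3. Adjust for baseline, either as a covariate by visit or as a response whose mean is equal in both arms.

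The first two are less efficient than the third under the assumptions below, and they handle chance baseline imbalance less well. The text does not say which is meant.

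The outcome lists raise a different problem. Two self-reported scales in an unblinded trial are secondary in two sections and absent from the section that defines the outcomes. Analysis plans written from these sections would test different sets of outcomes.

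**Working it through.** **Inputs.** From Sample size calculation: SD 3.5, difference 2 points, α 0.05, power 90%, 66 per group before dropout, 30% dropout. The documents give no correlation r between baseline and follow-up, so r = 0.3, 0.5 and 0.7 are assumptions. Further assumptions are equal variance at baseline and follow-up, and SD 3.5 with 66 per arm at each follow-up visit.

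**The plan's own figure.** Two-sided normal approximation: n = 2 × (1.960 + 1.282)² × 3.5² / 2² = 64.4, so 65 per arm. The t-based calculation gives power 0.899 at 65 and 0.903 at 66, so 66 reproduces. With dropout, 66 / 0.7 = 94.3, stated as 94.

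**Precision at one follow-up visit.** The standard error without baseline is 3.5 × √(2/66) = 0.609, and the 95% half-width is 1.96 × 0.609 = 1.19 points. With baseline as covariate, multiply by √(1 − r²). For unconstrained change from baseline, multiply by √(2(1 − r)). The model with baseline as a response and equal arm means was computed by generalised least squares with four visits and compound symmetry.

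| Half-width, HADS-D points | r = 0.3 | r = 0.5 | r = 0.7 |
|---|---|---|---|
| Baseline unused | 1.19 | 1.19 | 1.19 |
| Unconstrained change | 1.41 | 1.19 | 0.93 |
| Baseline as covariate | 1.14 | 1.03 | 0.85 |
| Baseline as response, equal means | 1.14 | 1.03 | 0.85 |
| Unused vs covariate, 1/√(1 − r²) | 5% wider | 15% wider | 40% wider |
| Change vs covariate, √(2/(1 + r)) | 24% wider | 15% wider | 8% wider |

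**If baseline spread is restricted.** Entry requires a score of at least 8 on one HADS subscale or both, which may narrow the baseline distribution. With baseline SD equal to k times the follow-up SD, the variance ratio of change to covariate adjustment is (1 + k² − 2rk)/(1 − r²). For an assumed k = 0.7:

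- r = 0.3: (1.49 − 0.42)/0.91 = 1.18, against 2/(1 + 0.3) = 1.54 with equal variances.
- r = 0.5: (1.49 − 0.70)/0.75 = 1.05, against 1.33.

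The loss from leaving baseline out, 1/(1 − r²), does not depend on k.

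**Counting comparisons (cost outcomes excluded).**

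- Secondary objectives: 5 at 3 months (including dropout) + 5 × 2 later visits = 15.
- Trial outcomes: 1 (anxiety at 3 months) + 4 (depression and anxiety at two visits) + 3 (HeartQoL) + 1 (dropout) = 9.
- Difference: 15 − 9 = 6, which is two scales at three visits.
- Secondary comparisons under the mixed model: HADS anxiety and HeartQoL at 3 months (2), plus HADS depression, HADS anxiety and HeartQoL at 6 and 12 months (6) = 8.

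**The case against.** The strongest reply is that the text does not show any loss. A model of change over time with within-patient correlation, for scales measured at baseline, is compatible with baseline as a repeated response with equal arm means, and that version matches covariate adjustment exactly. The confounder sentence also treats baseline as a standing adjustment variable alongside the strata, which weakens any inference that it was deliberately dropped. The coding of a secondary mixed model is ordinary analysis-plan content, and this is a condensed article. All of that stands as a reason not to assert a loss. It does not remove the point that the article chose to state an adjustment set for this model, and that the set differs from the one for the primary model.

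Stronger readings are tempting, and the documents do not support them:

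- *Precision is lost for nearly all secondary results.* The model covers 8 of the 15 comparisons in Secondary objectives. It covers 8 of 9 only on the shorter list.
- *The results will be biased.* Under randomisation, leaving baseline out costs precision and leaves chance imbalance uncorrected. It does not bias the comparison systematically.
- *Two 3-month depression estimates make the primary result ambiguous.* They could differ, but the linear regression is explicitly designated as primary.
- *Perceived stress and health complaints will go unanalysed or be reported selectively.* Both are declared in the abstract and objectives and scheduled at every visit. Naming HADS and HeartQoL for one model does not say that the other scales have none.

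The unseen analysis plan does not answer the outcome-list conflict, because that is a disagreement between sections of one document.

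**Conclusion.** There are two conclusions of different firmness.

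The outcome-list conflict is certain: two scales are secondary at three visits in the abstract and objectives and missing from Trial outcomes, a difference of six comparisons.

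The baseline point is conditional. The stated adjustment for the mixed model is narrower than for the primary model. The resulting loss ranges from none (baseline as a response with equal means) through 8–24% in interval width (unconstrained change) to 5–40% (baseline unused). Those ranges rest on assumed correlations of 0.3 to 0.7; the change-score range also needs equal variances, and it shrinks if baseline spread is restricted. At r = 0.5 the difference is a half-width of 1.19 against 1.03 points, beside a minimal important difference of 2.

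Only secondary precision and sensitivity to chance imbalance are affected. The primary analysis already adjusts for baseline, and the sample size stands. The point is worth correcting but does not threaten the main result.

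**What to change.** 1. State in Statistical methods that the mixed model includes arm by visit, the strata (site and stable versus unstable IHD), and the baseline score by visit; or, equivalently for precision, baseline as a response with equal arm means.
2. Reconcile the abstract, Secondary objectives and Trial outcomes so that one list of secondary outcomes holds throughout.
3. Apply the same model to every continuous secondary outcome retained, including the Perceived Stress Scale and the Health Complaints Scale.

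The cost is wording only. Table 3 already schedules all four measures at baseline and every follow-up. At the status date in the article (17 December 2020) 31 of 188 patients were included, the first on 22 May 2020, so no 12-month outcome could yet have been observed. If the analysis plan already settles these points, the article's text should be brought into line with it.

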### Eligibility and recruitment

Consecutive patients referred to CR with IHD, ≥18 years of age, with a diagnosis of IHD (codes I20-I25), HADS score ≥ 8 on depression, anxiety or both, with access to a computer or smartphone, ability to use a computer or smartphone, and proficient in the Danish language are eligible for inclusion. Patients with severe psychiatric disorders (i.e., borderline disorder, schizophrenia or bipolar disorder), severe cognitive difficulties (e.g. severe brain damage, mental retardation, or dementia) that will prevent patients from participating, endorsement of suicidal ideation with daily suicidal thoughts (PHQ-9 item 9 > 2), participating in other intervention studies (unless they are clinical studies [e.g. medication trials]), or seeing a psychologist or mental health professional for the treatment of depression and anxiety, will be excluded (Fig. 1). Patients who were previously enrolled in the study and referred to CR due to a new cardiac event will not be eligible to participate a second time. Table 1 presents an overview of the recruitment procedure.

**Table 1 Tab1:** Overview of recruitment procedure

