## Sample size calculation

Based on Stauber et al. [34], a conservative estimate of the standard deviation of the mean of the HADS depression score at 3 months is 3.5. The minimal clinically important difference for the HADS is 2 points [35]. For a normal-based comparison of independent means, with a power of 90% (ß = 0.1) and a risk of Type 1 error of 5% (α = 0.05), the estimated required number of patients is *n* = 66 in each group. Considering a potential 30% dropout rate, the estimated number of needed participants is *n* = 94 patients in each group (n (total) = 188).

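### The age subgroup analysis of the primary outcome is fixed as a median split, which costs power if the treatment effect changes roughly linearly with age and leaves the cut-point in years undefined until enrolment ends

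*Protocol article*

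**What the plan says.** The Statistical methods section of the protocol article says that "Pre-planned subgroup analyses will be conducted for the primary outcome with respect to" type of IHD, sex, age and baseline depression status. Age is given only as "age (median split", with no age in years. The baseline depression item in the same list does use numeric HADS cut-points.

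The model for the primary endpoint is given just before: "The primary analysis will be a linear regression of depression scores at 3 months including randomisation group and strata as factors", with the baseline depression score as covariate. HADS depression is therefore analysed on its full scale.

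Eligibility requires patients to be "≥18 years of age" and able to use a computer or smartphone. The article gives no age distribution and describes no analysis with age as a continuous modifier. It also does not say how subgroup effects will be compared.

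**The concern.** A median can be computed only if age is held as a number, so the full information is there and the split sets part of it aside. A patient just below the median is treated as unlike one just above it, but as identical to the youngest patient in the trial.

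The cut is also a rule without an age. Its value is known only once the sample is known, so younger and older have no meaning that can be stated in advance or matched to another trial.

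Age is a natural modifier for a programme delivered by computer or smartphone. A trial sized for a main effect has little power for effect modification to begin with. If benefit rises or falls steadily with age, the split makes that trend easier to miss.

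**Working it through.** **Inputs from the article (Sample size calculation).**
- SD: "a conservative estimate of the standard deviation of the mean of the HADS depression score at 3 months is 3.5". This is read as the SD of individual scores, because that reading reproduces the stated sample size.
- Difference: "The minimal clinically important difference for the HADS is 2 points".
- Power 90%, type I error 5%, dropout 30%, allocation 1:1.

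**Assumptions, not in the article.** Subgroups are compared with a two-sided 5% interaction test. Age shape and the form of effect modification are assumed as stated at each step.

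**1. The plan's own figure.** n per group = 2 × [3.5 × (1.960 + 1.282) / 2]² = 64.4, so 65 by the normal formula. The t-test version gives 65.3, so 66, as stated. 66 / 0.70 = 94.3, stated as 94 per group and 188 in total. The sample size reproduces, and the evaluable number is 2 × 66 = 132.

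**2. Information lost by the split.** For an effect linear in age, the share lost is 1 − r², where r is the correlation between age and the above-median indicator.

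| Assumed age shape | Share lost |
|---|---|
| Uniform | 25% |
| Normal (1 − 2/π) | 36% |
| Normal truncated at 18 (mean 63, SD 11 assumed) | 36% |
| Moderately left-skewed | 39% |
| Heavy-tailed | 46% to 50% |

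Under normal age, 132 patients work like 132 × 2/π = 84.

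**3. Power by formula, normal age, 2-point difference between the halves.**
- Split: each of four cells holds 132/4 = 33 patients. SE = 3.5 × √(4/33) = 1.22. Power = Φ(2/1.22 − 1.96) = 37%.
- Continuous: the means of the halves lie 2√(2/π) = 1.596 SD of age apart, so the slope is 2/1.596 = 1.253 points per SD. SE = 3.5/√(132 × 0.25) = 0.609. Power = Φ(1.253/0.609 − 1.96) = 54%.

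**4. Power by simulation.** There were 6,000 to 8,000 trials per scenario, with 132 patients, SD 3.5, and terms for treatment, modifier and their product. Baseline score and strata were left out.

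| Age shape and form of effect | Difference between halves | Continuous age | Median split |
|---|---|---|---|
| Normal, linear | 0 | 5% | 5% |
| Normal, linear | 2 | 52–53% | 36% |
| Normal, linear | 3 | 84–85% | 65% |
| Normal, linear | 4 | 98% | 87% |
| Uniform, linear | 2 | 45% | 36% |
| Uniform, linear | 3 | 79–80% | 66–67% |
| Normal, step at the population median | 2 | 25% | 33% |
| Normal, step at the population median | 3 | 48% | 62% |

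Under a linear trend, continuous age gains roughly 10 to 20 percentage points. Under a step at the median, it loses 8 to 14.

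**The case against.** The strongest objection is that this is a preference for a more efficient secondary analysis. The rule is set in advance, cannot be tuned to the outcome data, gives near-equal groups and keeps type I error at 5%. That all stands, and it is why the point is minor. It does not remove the point, because the split is a choice the article states and a better one is available at almost no cost.

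A second objection is that the article names no interaction test. How the subgroups are compared, and whether a continuous-age analysis is added, may be set out in an analysis plan that is not shown. This stands too, so the power figures are conditional on such a test. For the same reason, the lack of a stated rationale for the cut is not held against the plan.

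Third, the advantage of continuous age depends on the shape of the effect. A threshold is plausible for digital ability, and a step at the median favours the split. That is the most favourable case for the split, so it limits the claim without reversing it.

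Fourth, with an average effect of 2 points, a 3-point difference between halves means about 3.5 versus 0.5 points, which is extreme. At a 2-point difference even continuous age has only about 53% power. This trial is unlikely to settle the question of age by either method.

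Finally, the simulation leaves out baseline score and strata. Its absolute powers are therefore not those of the full model, and the comparison between the two methods is the part to rely on.

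**Conclusion.** The point holds in a conditional form. If modification by age is tested with the planned split and the effect is roughly linear in age, the split loses about 36% of the information for normal age, and about 25% to 50% over the other shapes tried. At a 2-point difference between the halves, power is about 36% instead of about 53%. The subgroups also have no fixed meaning in years.

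A reader might infer more than the article supports:
- **That a third of the information is lost regardless.** The article gives no age distribution or form of effect, so the figure rests on assumptions.
- **That the split never has an advantage.** It does as well or better if the effect steps near the median.
- **That the cut is chosen from the outcome data.** It is a rule fixed in advance, and only its value in years is unknown.
- **That the trial's main result is weakened.** The primary regression keeps HADS depression on its full scale, and the sample size of 188 reproduces. Neither is affected.

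This is a worthwhile improvement to a secondary analysis and not a flaw in the trial's main conclusion.

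**What to change.** In Statistical methods, replace the median split with a treatment-by-continuous-age interaction in the primary regression model: randomisation group, strata, baseline HADS depression score, age, and group × age. Report the treatment effect with its 95% confidence interval at ages fixed in advance. Add a spline or quadratic term as a check on linearity, since a threshold effect is possible. If a two-group display is wanted, keep it descriptive and fix the cut in years beforehand.

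The cost is a sentence or two of analysis wording, with no new data or patients. The Trial status section reports 31 of 188 patients included at the time of writing. The one real downside is the linearity assumption, which the non-linearity check and the descriptive display address.
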